## Abstract

**Background:**

Poor sleep is prevalent in patients with systemic inflammatory disorders, including rheumatoid arthritis, and, in addition to fatigue, pain, depression and inflammation, is associated with an increased risk of co-morbidity and all-cause mortality. Whereas non-pharmacological interventions in patients with rheumatoid arthritis have been shown to reduce pain and fatigue, no randomized controlled trials have examined the effect of non-pharmacological interventions on improvement of sleep in patients with rheumatoid arthritis. The aim of this trial was to evaluate the efficacy of an intermittent aerobic exercise intervention on sleep, assessed both objectively and subjectively in patients with rheumatoid arthritis.

**Methods/design:**

A randomized controlled trial including 44 patients with rheumatoid arthritis randomly assigned to an exercise training intervention or to a control group. The intervention consists of 18 session intermittent aerobic exercise training on a bicycle ergometer three times a week. Patients are evaluated according to objective changes in sleep as measured by polysomnography (primary outcome). Secondary outcomes include changes in subjective sleep quality and sleep disturbances, fatigue, pain, depressive symptoms, physical function, health-related quality of life and cardiorespiratory fitness.

**Discussion:**

This trial will provide evidence of the effect of intermittent aerobic exercise on the improvement of sleep in patients with rheumatoid arthritis, which is considered important in promotion of health and well-being. As such, the trial meets a currently unmet need for the provision of non-pharmacological treatment initiatives of poor sleep in patients with rheumatoid arthritis.

**Trial registration:**

ClinicalTrials.gov Identifier: NCT01966835

## Background

Restorative sleep has an important role in maintaining health [1], with disrupted or lower levels of sleep being related to serious outcomes such as increased risk of morbidities [2,3] and ultimately all-cause mortality [4]. Sleep disturbances and poor sleep quality are prevalent complaints in patients with chronic diseases [5] including rheumatoid arthritis (RA). RA is a chronic inflammatory disease associated with increased mortality, high morbidity and reduced health related quality of life [6,7]. It affects between 0.1 and 0.5% of adults in developed countries and is three times more frequent in women than men. In addition to pain and fatigue, poor sleep has been identified as a major concern by patients with RA [8] affecting 50-70% of the patients [9]. Importantly, poor sleep in RA may be affected by pain or may contribute to increased pain and fatigue [10-13], and is associated with depression [14,15] and inflammation [16]. Thus, addressing poor sleep quality may be important in promoting health and well-being in patients with RA.

Few studies have examined treatments for managing poor sleep in patients with RA. Those carried out have examined sleep medication (eszopiclone, zopiclone, valerian) [17-19] or biological therapies (tocilizumab, infliximab, anti-tumor necrosis factor α, abatacept) [20-23]. However, non-pharmacological psychological interventions (e.g. cognitive behavioral therapy) [24] have been shown to be an effective alternative for patients with sleep disturbances and may have a longer-lasting effect, with no side effects. However, psychological interventions (e.g. cognitive behavioral therapy) typically require highly skilled clinicians and may therefore be expensive and time-intensive to deliver [24]. Also, while psychological interventions are promising, they mainly affect mental health and/or include low-intensity behavioral interventions (e.g. relaxation) with little or no effect on functional and physiological outcomes.

Cross-sectional studies have shown that physical inactivity increases the likelihood of reporting poor sleep, even after controlling for age, depression and pain [25,26]. Furthermore, it has been reported that, independent of age and sex [27], maximal aerobic capacity is lower in patients with insomnia compared to those without it. In addition, physical exercise interventions have been shown to be a feasible and effective non-pharmacological treatment modality for improving sleep in healthy and in clinical populations [28-31]. Exercise interventions is known to improve cardiorespiratory fitness, muscle strength and functional ability [32], as well as health-related quality of life [33], and to reduce co-morbidity [34] in patients with RA. Thus, physical exercise interventions may be a viable non-pharmacological alternative for both prevention and treatment of poor sleep in addition to the simultaneous benefits for numerous health parameters in the human body.

The effect of physical exercise interventions on poor sleep has not hitherto been examined in patients with RA. However, a systematic review including older adults has shown that exercise of moderate intensity has a moderately positive effect on improvement of self-reported sleep [31]. In addition, a randomized controlled trial (RCT) [35] of adults > 55 years old found that moderate intensity exercise decreased objectively measured Stage 1 sleep and number of nighttime awakenings, and increased Stage 2 sleep. However, high-intensity aerobic exercise may also be assumed to be efficient for improving sleep. For patients who do not possess the necessary fitness level to perform continuous high-intensity exercise, aerobic intermittent training (defined as: vigorous exercise performed at a high intensity for a brief period of time interposed with recovery intervals at low to moderate intensity [36]), may provide an alternative to continuous high-intensity exercise.

In summary, the significant morbidity associated with poor sleep and the multifactorial impact of physical exercise suggest that an intermittent aerobic exercise training intervention may constitute a promising non-pharmacological treatment approach for the management of poor sleep in patients with RA.

Against this background, the aim of this trial is to assess the efficacy of an aerobic intermittent exercise training intervention on sleep quality and sleep disturbances in patients with RA. The primary hypothesis is that intermittent aerobic exercise will be superior to no exercise in the improvement of objectively measured sleep. The secondary hypotheses are that patients randomly assigned to the exercise intervention will show greater improvement in subjective sleep quality and sleep disturbances, cardiorespiratory fitness, and physical function as well as reduced pain, fatigue and depressive symptoms and improved health-related quality of life compared to patients randomly assigned to the no-intervention (control group).

## Methods

### Design

The present RCT is single blinded, with an aerobic intermittent exercise training intervention and a primary endpoint of sleep measured by polysomnography (PSG). Flow of patients through the trial is shown in Figure 1.

**Figure 1 F1:**
[figure not shown]
Flow of patients through the randomized controlled trial.

#### Sample size

The sample size calculation is based on the sleep component `sleep efficiency´. A previous RCT [37], using PSG as measurement of sleep, examined the effect of a non-pharmacological intervention (cognitive behavioral therapy) on sleep disturbances in patients with insomnia and found a mean sleep efficiency of 81.4% (SD 7.4). The normal value for sleep efficiency is >85%. Thus the aim for the patients in the exercise intervention was to achieve a sleep efficiency of at least 86%. On this basis, and with a significance level of α = 5% and a power of 80%, it is estimated that 36 patients should take part in this trial. A drop-out rate of 20% is expected, which means that 44 patients are included, of which 22 are randomly assigned to the intervention group and 22 to the control group.

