#### Randomization and blinding

Included patients are randomly assigned to one of the two following conditions: aerobic intermittent training (n = 22) or control group (n = 22). Randomization is performed by computer-generated `random numbers´ with a 1:1 allocation ratio. Evaluation of primary outcome is performed by experienced polysomnographic technicians who are blinded to group allocation.

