### Assessment of primary endpoint

The primary outcome of the trial is changes in sleep as measured objectively by PSG at baseline and at the end of the intervention. PSG measurements are performed at the patient’s home in order for them to sleep in familiar surroundings. However, the primary investigator performs electrode placement and tests the equipment at Glostrup Hospital. Sleep monitoring is performed using Trackit™ Ambulatory EEG (Lifelines Ltd, [name]). The evaluation of the PSG measurements is performed following the guidelines of the American Academy of Sleep Medicine (AASM standard) 2007 [39].

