### Statistical analyses

Continuous variables, i.e., sleep, cardiorespiratory fitness, physical function, pain, fatigue, depressive symptoms and health-related quality of life will be presented as either means with corresponding 95% confidence limits or as medians and interquartile range (IQR). The primary and secondary endpoints will be reported as a two-sample t-test comparing change scores in the two randomized groups. The primary outcome variables in the regression model will be sleep parameters. The regression model will allow control for the baseline value of the trial endpoints and other confounding variables that may impact changes in sleep parameters (e.g. age and gender). Categorical data, i.e., single questionnaire items, will be reported as proportions and compared across randomized groups using chi-squared tests or logistic regression. Significance level will be set at 0.05. All tests will be two-tailed. The primary analysis will compare changes in the intervention vs. the control group using the intention-to-treat principle including all available data. Missing observations will be handled according to the missing at random assumption. The secondary analysis will include only patients attending at least 14 exercise sessions (80%) out of the prescribed 18 (i.e. per protocol analysis). Finally, correlations will be performed to examine the dose-response relation between changes in the primary outcome (sleep) and cardiorespiratory fitness. Data entry will be undertaken using a secure web server and statistical analysis will be performed using Statistical Analysis Systems (SAS) version 9.3.

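### The sample size uses the SD of a sleep-efficiency level while the planned test compares changes, so the stated power is not on the analysed scale; the error can go in either direction

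*Protocol article*

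**What the plan says.** The Sample size section (protocol article) names sleep efficiency as the planning variable. It cites an earlier randomised trial in insomnia that "found a mean sleep efficiency of 81.4% (SD 7.4"). The target is also a level: "the aim for the patients in the exercise intervention was to achieve a sleep efficiency of at least 86" per cent. From these inputs, "with a significance level of α = 5% and a power of 80" per cent, it derives 36 patients, raised to 44 for drop-out.

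The outcome and the analysis are on another scale. The section headed Assessment of primary endpoint defines the outcome as a difference between two visits: "The primary outcome of the trial is changes in sleep as measured objectively by PSG at baseline and at the end of the intervention". Under Statistical analyses: "The primary and secondary endpoints will be reported as a two-sample t-test comparing change scores in the two randomized groups", and "All tests will be two-tailed". The same section also mentions an adjusted model: "The regression model will allow control for the baseline value of the trial endpoints and other confounding variables". Patients are randomised "with a 1:1 allocation ratio".

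The article gives neither an SD of change nor a correlation between the two visits, and nothing connects 7.4 to the change score or to the adjusted model.

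**The concern.** An SD reported beside a mean level describes how patients differ from one another at one measurement. A change score has a different SD, which depends on how strongly the two polysomnographies of the same patient agree. A power figure built on the first SD is therefore not, in general, the power of a test on the second.

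This matters because the claimed 80% describes what the trial can detect, and readers may lean on it when they interpret a null result in a trial of 44 patients. It also matters for the repair. The 36 patients do not follow from the stated inputs in a two-sample test. Someone who corrects only that arithmetic and keeps 7.4 would publish a new figure that is exact for the change-score test at one value of r only.

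**Working it through.** **Inputs.** From Sample size: mean 81.4%, SD 7.4, target 86%, alpha 5%, power 80%, 36 evaluable patients. From Statistical analyses: two-tailed, two-sample t-test on change. From Randomization and blinding: 1:1, so 18 per arm. Difference = 86 - 81.4 = 4.6 points, which treats 81.4 as the mean expected without exercise; the text does not say so, but no other comparator is given. The correlation r is not in the document and is an assumption, shown from 0.3 to 0.7.

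**Step 1: the plan's own figure.** Standardised difference = 4.6/7.4 = 0.62. A two-sided two-sample test at 5% needs 41 per arm for 80% power by the normal approximation and 42 by the t distribution, so 82 to 84 in total, not 36. With 18 per arm the power is 46% (normal) or 44% (t). This is the separate arithmetic error. The figures below use the noncentral t.

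**Step 2: the change-score t-test.** With equal variances at both visits, SD(change) = 7.4 x sqrt(2(1 - r)).

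| r | SD of change | Power, 18 per arm | Per arm for 80% |
|---|---|---|---|
| 0.3 | 8.76 | 33% | 58 |
| 0.5 | 7.40 | 44% | 42 |
| 0.7 | 5.73 | 65% | 26 |

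**Step 3: the baseline-adjusted regression.** Residual SD = 7.4 x sqrt(1 - r^2), which is below 7.4 for any non-zero r.

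| r | Residual SD | Power, 18 per arm |
|---|---|---|
| 0.3 | 7.06 | 48% |
| 0.5 | 6.41 | 55% |
| 0.7 | 5.28 | 72% |

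**Step 4: what 80% with 36 would require.** At 18 per arm, 80% power needs a standardised difference of 0.961, so an SD of change of 4.6/0.961 = 4.79. Then r = 1 - (4.79/7.4)^2/2 = 0.79. No such value is stated.

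**Step 5: separating the two faults.** The fall from 80% to 44% arises with SD 7.4 kept as it stands, so it belongs to the arithmetic. The part due to the scale is the move away from 44%: down 11 points at r = 0.3 and up 21 points at r = 0.7 for the change-score test, and up 4 to 28 points for the adjusted regression.

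**Step 6: the effect of correcting the arithmetic alone.** With 42 per arm, the change-score test has 66% power at r = 0.3, 80% at r = 0.5 and 95% at r = 0.7. The adjusted regression has at least 84% throughout r = 0.3 to 0.7.

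**The case against.** A reader might infer that the mismatch makes the trial weaker still, because r is likely to be below 0.5. The document does not support this. It contains nothing about r, and above 0.5 the sign reverses, so that 7.4 overstates the SD of change. For the baseline-adjusted regression, 7.4 is conservative at any non-zero r. Only the unadjusted change-score test with r below 0.5 is harmed.

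A reader might also infer that correcting the arithmetic could not mend the power statement. That is too strong. A size corrected with SD 7.4 falls short of 80% only for the unadjusted test with r below 0.5 (Step 6). What remains true is that the corrected figure would still not be shown to belong to the analysis that is run.

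A third argument is that a condensed article may leave r to a fuller document. This does not remove the point. The article states its inputs and derives 36 from them, so the conflict lies between things it says rather than in something it omits. It is fair to add that the article does not say at which visit or in which arm 7.4 was measured; that it is the SD of a level follows from its being reported with a mean level.

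Finally, a null result is better read from the confidence interval for the group difference than from planning power. That is right and limits the weight of this point, but a stated power should still describe the planned test.

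**Conclusion.** The point holds as a mismatch of scale without a fixed direction. The stated power is not shown to be that of the planned change-score test. Relative to the 44% that SD 7.4 gives with 18 evaluable per arm, the change-score test runs from 33% to 65% over r = 0.3 to 0.7, and the baseline-adjusted regression from 48% to 72%. The arithmetic error is the larger and firmer fault. Even so, neither analysis reaches 80% with 36 evaluable patients anywhere in that range.

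This rests on a 4.6-point difference, equal variances at both visits, 7.4 being the SD of a level, and an assumed range for r. It deserves correction because the repair is cheap and the figure is one that readers may rely on. It does not show that the scale mismatch by itself leaves the trial underpowered.

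**What to change.** When the power statement is corrected, put it on the scale that is analysed:

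- Name the analysis that decides the primary comparison. The baseline-adjusted regression already mentioned under Statistical analyses is preferable, because 7.4 is then a conservative SD and power is higher than for the change-score test at each r shown.
- Give the SD that belongs to that analysis: 7.4 x sqrt(1 - r^2) for the regression, or 7.4 x sqrt(2(1 - r)) for the change-score t-test. State the assumed r and its basis.
- Restate the power of the planned 44 (about 36 evaluable) over r = 0.3 to 0.7 in place of the single 80%.
- If the assumed r is checked at the end of the trial, use the within-arm correlation. A correlation pooled over arms can be distorted by a treatment effect.

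The cost is a few sentences and a less favourable stated power. No extra patients are needed.

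### The stated inputs (81.4% vs 86%, SD 7.4, two-sided 5%, 80% power) need 84 evaluable patients, not 36; taken at face value, 36 patients give about 44% power

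*Protocol article*

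**What the plan says.** The Sample size section of the protocol article bases the calculation on sleep efficiency measured by polysomnography. It reports that an earlier randomised trial of cognitive behavioural therapy in insomnia "found a mean sleep efficiency of 81.4% (SD 7.4"). It then sets the target: "the aim for the patients in the exercise intervention was to achieve a sleep efficiency of at least 86" per cent. On that basis, with 5% significance and "a power of 80%, it is estimated that 36 patients should take part in this trial". The final step is the allowance for losses: "A drop-out rate of 20% is expected, which means that 44 patients are included", 22 in each group.

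The rest of the design is fixed elsewhere in the article. Randomization and blinding says that allocation is "with a 1:1 allocation ratio", so 36 patients means 18 per arm. Statistical analyses says that endpoints are reported as a "two-sample t-test comparing change scores in the two randomized groups", mentions a regression model that controls for baseline, and adds "All tests will be two-tailed". No section gives an SD of change or a correlation between baseline and follow-up.

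**The concern.** The article prints both the inputs and the result, so the calculation can be repeated. A difference of 4.6 points against an SD of 7.4 is a moderate standardised effect, and 18 patients per arm is far too few to detect an effect of that size with 80% power.

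There is a second mismatch. The SD of 7.4 describes sleep efficiency as a level in another population, whereas the planned test compares changes. The variance that matters for the test was therefore never specified.

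This paragraph is the only justification for the size of the trial. If the power is well below 80%, readers are told that the trial can reliably detect an effect which, on the stated inputs, it would miss more often than not. A non-significant result could then be read as evidence that exercise does not improve sleep in rheumatoid arthritis, when the trial was simply too small to tell.

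**Working it through.** **Inputs**

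| Input | Value | Section |
|---|---|---|
| Reference mean | 81.4% | Sample size |
| Target mean, exercise | 86% (the minimum aimed for) | Sample size |
| SD | 7.4 points | Sample size |
| Significance level, power | 5%, 80% | Sample size |
| Sidedness | two-sided | Statistical analyses |
| Allocation | 1:1 | Randomization and blinding |

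The article does not say outright that 81.4% is the expected control mean. It is the only mean given, so it is taken as such here.

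**1. Trying to reproduce 36**

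Difference = 86 − 81.4 = 4.6; d = 4.6/7.4 = 0.622.

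Normal approximation: n per arm = 2(1.960 + 0.842)²/0.622² = 40.6, so 41 per arm and 82 in total. The exact t-test (noncentral t) gives 41.6, so 42 per arm and 84 in total.

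Other readings, each at 80% power:

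- One-sided two-sample t-test: 32.7, so 33 per arm and 66 in total.
- Target of 85% (difference 3.6), two-sided, normal approximation: 134 in total.
- Difference of 5.0, two-sided, normal approximation: 70 in total.
- One-sample two-sided t-test: 22.3.
- One-sample one-sided t-test: 17.4, so 18; doubled for two arms, this is 36.

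The last is the only route found to 36. Whether it was used is conjecture. It treats the comparison value as known without error and is one-sided, so it is not valid for a two-tailed comparison of two randomised groups.

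**2. Power of the planned trial on the stated inputs**

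| Evaluable per arm | Exact t-test | Normal approximation |
|---|---|---|
| 18 (36 in total) | 44.1% | 46.2% |
| 22 (44 in total, no losses) | 52.2% | 54.1% |

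For 80% power at 18 per arm, d must be 0.961. At SD 7.4 that is 0.961 × 7.4 = 7.1 points (81.4% to 88.5%). At a difference of 4.6 it requires an SD of 4.6/0.961 = 4.8.

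**3. Change scores and baseline adjustment**

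Suppose 7.4 is the SD at a single time point and r is the baseline-to-follow-up correlation. The SD of change is then 7.4√(2(1 − r)), and the SD after baseline adjustment (ANCOVA) is 7.4√(1 − r²). The article gives no r, so a range is assumed. Power at 18 per arm:

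| r (assumed) | Change-score t-test | ANCOVA |
|---|---|---|
| 0.3 | 33% | 48% |
| 0.5 | 44% | 55% |
| 0.7 | 65% | 72% |

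Reaching 80% with 36 patients needs r of about 0.79 for change scores or 0.76 for ANCOVA. If 7.4 were itself the SD of change, power would again be 44%.

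**4. Allowance for losses**

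36/0.8 = 45, and 44 × 0.8 = 35.2. The stated 44 falls one patient short, which is immaterial beside the main discrepancy.

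**The case against.** The strongest defence is that 44% is conditional. The plan analyses change and also allows for baseline in a regression, so with a high enough correlation the power is better: 72% with ANCOVA at r = 0.7 and 18 per arm, and about 80% at r = 0.7 if all 44 patients are evaluable. On some of these combinations the trial is not more likely than not to miss its target. This is correct. The 44% should be presented as the result of the stated inputs at face value, alongside the range over r. It does not rescue the figure of 36, because the article derives that figure from a mean, an SD, a significance level and a power alone. The favourable 80% case also assumes no losses, although the plan expects 20%.

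It can also be said that 81.4% is never labelled as the control mean and that 86% is a minimum. Both are fair, but no other contrast can be formed from the figures given.

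Borrowing an SD from another population is ordinary practice and is disclosed, so it is not a fault in itself. The loss allowance is trivial, as shown above. Finally, an article may leave detail to a fuller protocol, but here the result contradicts the inputs printed beside it. If another assumption was used, the paragraph misstates the basis of the calculation.

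**Conclusion.** The concern holds. For the two-sided two-sample t-test in the plan, the stated inputs require 84 evaluable patients, more than twice the 36 given. Power at 36 is about 44% rather than 80%, and the difference detectable with 80% power is 7.1 points rather than 4.6.

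This rests on 81.4% being the control mean and on 7.4 being the SD of the quantity analysed. If 7.4 is instead the SD of a level, power at 36 runs from 33% to 65% for change scores and from 48% to 72% for ANCOVA as r goes from 0.3 to 0.7, all below the stated 80%. Only an unstated correlation of about 0.76 or more would support the claim. The power statement for the primary hypothesis is wrong as written and must be corrected.

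**What to change.** Rewrite the sample size paragraph in one of two ways.

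- **Keep the stated inputs and report what they give:** 36 evaluable patients have about 44% power for a difference of 4.6 points at SD 7.4, or 80% power for about 7.1 points.
- **If a correlation or SD of change was used,** state it with its source, base the calculation on the baseline-adjusted analysis, and show power over a range. At 18 per arm this is 48%, 55% and 72% for r = 0.3, 0.5 and 0.7.

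In either case, say that 81.4% is the assumed control mean. Tidy the loss allowance by stating either 45 patients for a 20% loss or an 18% loss for 44 (8/44 = 18%). Commit to interpreting the between-group difference by its 95% confidence interval, so that a non-significant result is not reported as absence of effect.

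The cost is one paragraph of rewording and a less favourable stated power. The correction itself needs no extra enrolment. The article says recruitment was still under way at submission.

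### Including 44 patients does not quite cover the stated 20% drop-out: a 20% loss leaves about 35 of the 36 patients needed, and 44 allows for a loss of about 18%

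*Protocol article*

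**What the plan says.** The Sample size section of the protocol article first gives the number required for its stated significance level and power: "it is estimated that 36 patients should take part in this trial". It then allows for loss and arrives at the number to enrol: "A drop-out rate of 20% is expected, which means that 44 patients are included". It divides that number equally between the arms: "44 patients are included, of which 22 are randomly assigned to the intervention group and 22 to the control group". The wording presents 44 as what follows from 36 and 20%, but no formula is shown.

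The same size appears in the Abstract and under Population. Under Randomization and blinding it is given as 22 per group, "with a 1:1 allocation ratio". The Trial status section says that patients were being recruited when the manuscript was submitted.

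**The concern.** A drop-out rate is normally a share of the patients who are included. To finish with a required number, one divides that number by the share expected to remain. On that understanding the total should be at least 45, and 44 falls short of the allowance that the article says it makes.

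What is at stake is whether the stated enrolment delivers the plan's own evaluable number at the plan's own loss rate. All three figures (36, 20% and 44) are in the article, so the check does not depend on a fuller protocol or an analysis plan.

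**Working it through.** **Inputs, all from the Sample size section:** required number 36, drop-out 20%, included 44 (22 per arm). The 1:1 allocation, from Randomization and blinding, makes the required number 18 per arm.

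**Step 1. Reproduce 44.** Two routes give it:
- Multiply the total by 1.2: 36 × 1.2 = 43.2, rounded up to 44. This amounts to taking 20% of the 36 (7.2, rounded up to 8) and adding it.
- Divide per arm and round down: 18/0.8 = 22.5, rounded down to 22, and 2 × 22 = 44.

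The article does not say which was used, if either.

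**Step 2. Apply the stated loss to 44.**
- Total: 44 × (1 − 0.20) = 35.2, against 36.
- Per arm: 22 × 0.80 = 17.6, against 18.
- In whole patients, losing 8 leaves 36 (8/44 = 18.2%). Losing 9 leaves 35 (9/44 = 20.5%).

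So 44 allows for a loss of 18.2%.

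**Step 3. The number that leaves 36.**
- Total: 36/(1 − 0.20) = 45.
- Equal arms: 18/0.80 = 22.5, rounded up to 23 per arm, so 46.

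The gap is 1 to 2 enrolled patients.

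**Step 4. Cost in power.** Suppose that 36 patients gave exactly 80% power in a two-sided 5% test. The two-sided choice is from Statistical analyses: "All tests will be two-tailed". By the normal approximation the standardised effect at 18 per arm is 1.960 + 0.842 = 2.802, and it scales with the square root of the number per arm.
- At 17.6 per arm: 2.802 × √(17.6/18) = 2.770. Power = Φ(2.770 − 1.960) = 0.791.
- At 17.5 per arm (35 patients): 2.802 × √(17.5/18) = 2.762. Power = Φ(2.762 − 1.960) = 0.789.

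The loss is about 1 percentage point.

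**Step 5. What this check does not cover.** Step 4 takes 36 as given. Now take the quoted mean of 81.4% as the control value, 86% as the exercise target, and 7.4 as the SD of the quantity compared. Then the difference is 86 − 81.4 = 4.6, and the number per arm is 2 × (2.802)² × (7.4/4.6)² = 40.6, rounded up to 41. That is 82 in total (84 by the t distribution). A high baseline to follow-up correlation would lower this. A change-score comparison needs 42 at a correlation of 0.75 and 34 at 0.80, and a baseline-adjusted comparison needs 36 at 0.75. The article states no correlation, so these values are assumptions. The base figure is a separate question from the drop-out step.

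**The case against.** The strongest case against raising this is that it is a rounding matter. A 20% drop-out is a round forecast, and 44 tolerates 18.2%. The shortfall is 0.8 of an evaluable patient. An allowance set at the expected loss does not guarantee the target under any formula. If patients drop out independently with probability 20%, the chance of keeping at least 36 is about 47% with 44 included, and still only about 59% with 45 and 69% with 46. All of this stands, and it keeps the point at the lowest level of importance. It does not make the sentence correct, because the article ties 44 to a 20% loss and 44 does not meet it.

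A reader might infer that the plan multiplied by 1.2 where it should have divided by 0.8. The figure fits, but the article shows no such step, and rounding 22.5 per arm down gives the same 44. The cause has to be left open. The shortfall is the same either way.

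A reader might also infer that the drop-out step leaves the trial materially underpowered, or that the error will grow in a larger trial. A cost of about 1 point does not support the first. The second would apply a rule that the article does not state to a sample size that it does not contain.

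**Conclusion.** The point holds, and it is minor. With 44 included and 20% lost, 35.2 patients remain, against the 36 that the article says it needs. The total that meets the stated allowance is 45, or 46 in equal arms. The cost is less than one evaluable patient and about 1 point of power (about 79% against 80%).

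This rests on three assumptions: that the rate is a share of those included, that losses fall evenly on the two arms, and, for the power figure only, that 36 evaluable patients give exactly 80%.

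It would be wrong to conclude that enrolling 45 or 46 secures the planned power. The article does not show how 36 follows from its stated means and SD, and correcting the drop-out step leaves that question untouched.

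**What to change.** Restate the sentence in the Sample size section along these lines: *including 44 patients allows for a drop-out of up to 18% (8 patients)*. This changes one sentence and needs no extra enrolment. The 44 and the 22 per group given elsewhere stay as they are. The only cost is that the stated tolerance becomes slightly less favourable.

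If the sample size is restated for any reason, compute the number to enrol as n/(1 − drop-out rate) and round up in each arm. Keeping the 20% allowance for 36 evaluable patients would mean 46 in equal arms. That is 2 more patients in a trial already recruiting, for about 1 point of power, and it would not by itself establish 80% power.
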